## Abstract

**Background:**

Globally, suicide is among the leading causes of death, with men being more at risk to die from suicide than women. Research suggests that people with suicidal ideation often struggle to find adequate help. Every month, around 4000 people fill in the anonymous self-test for suicidal thoughts on the website of the Dutch suicide prevention helpline. This self-test includes the Suicidal Ideation Attributes Scale (SIDAS), which educates users about the severity of their suicidal thoughts. The vast majority (70%) of people who complete the self-test score higher than the cutoff point (≥21) for severe suicidal thoughts. Unfortunately, despite this, less than 10% of test-takers navigate to the web page about contacting the helpline.

**Objective:**

This protocol presents the design of a web-based randomized controlled trial that aims to reduce barriers to contacting the suicide prevention helpline. The aim of this study is 2-fold: (1) to measure the effectiveness of a brief barrier reduction intervention (BRI) provided in the self-test motivating people with severe suicidal thoughts to contact the Dutch suicide prevention helpline and (2) to specifically evaluate the effectiveness of the BRI in increasing service use by high-risk groups for suicide such as men and middle-aged people.

**Methods:**

People visiting the self-test for suicidal thoughts on the website of the suicide prevention helpline will be asked to participate in a study to improve the self-test. Individuals with severe suicidal thoughts and little motivation to contact the helpline will be randomly allocated either to a brief BRI, in which they will receive a short tailored message based on their self-reported barrier to the helpline (n=388) or care as usual (general advisory text, n=388). The primary outcome measure is the use of a direct link to contact the helpline after receiving the intervention or control condition. Secondary outcomes are the self-reported likelihood of contacting the helpline (on a 5-point scale) and satisfaction with the self-test. In the BRI, participants receive tailored information to address underlying concerns and misconceptions of barriers to the helpline. A pilot study was conducted among current test-takers to identify these specific barriers.

**Results:**

The pilot study (N=1083) revealed multiple barriers to contacting the helpline. The most prominent were the belief that a conversation with a counselor would not be effective, fear of the conversation itself, and emotional concerns about talking about suicidal thoughts.

**Conclusions:**

Our study will provide insight into the effectiveness of a brief BRI designed to increase the use of a suicide prevention helpline provided in a self-test on suicidal thoughts. If successful, this intervention has the potential to be a low-cost, easily scalable, and feasible method to increase service use for helplines across the world.

**Trial Registration:**

ClinicalTrials.gov NCT05458830; https://clinicaltrials.gov/ct2/show/NCT05458830

**International Registered Report Identifier (IRRID):**

PRR1-10.2196/41078

## Introduction

According to the World Health Organization, suicide is among the leading causes of death worldwide, with more lives taken by suicide than by malaria, HIV/AIDS, breast cancer, or war and homicide. Globally, men are more likely to die from suicide than women, with a 2.3 times higher age-standardized suicide rate among males than females [1]. Unfortunately, research suggests that people with suicidal thoughts often do not seek help, making them invisible for preventive measures and targeted support [2-4]. Connecting individuals with suicidal ideation to appropriate mental health care services is, therefore, a key preventive effort.

A recently conducted systematic review by Tang et al [5] examined the factors associated with not using formal mental health services among individuals who died by suicide. They found the following key factors: male sex, both younger and older age, and living in a rural location. A subsequent systematic review by the same authors identified predictors of not receiving formal mental health services among people at risk of suicide. The findings of this review indicated that among people experiencing suicidality, minority ethnicity, better perceived general health, lower psychological distress, lower severity of suicidality, no mental health diagnosis, a lower perceived need for treatment, and lower use of medical services are all associated with nonreceipt of formal mental health services [6].

It is also assumed that a considerable percentage of people with suicidal ideation do not disclose their ideation. Studies among the general public in France and the Netherlands indicate that almost half of the adults with suicidal ideation do not disclose their thoughts about suicide to others [7,8]. And even when people are engaged in mental health care, disclosure of suicidality is not self-evident. A recent study among young Australians (aged 16-25 years) who had experienced suicidal ideation and were engaged with a mental health professional, revealed that 39% had never disclosed their suicidality to their clinician, with concerns about confidentiality as the most common reason [9].

In order to increase help-seeking behavior, it is important to have insight into the barriers that people experience when seeking help for suicidal thoughts. Known barriers to care are a lack of perceived need for services, the preference for self-management, fear of hospitalization, structural factors like time and finances, and stigmatizing attitudes toward suicide, mental health problems, and toward seeking professional treatment [3,10]. Another important issue is that of unmet mental health needs. Individuals may not receive the help they need because there are insufficient services available, they are unable to afford the cost of care, or they feel their treatment is not meeting their needs [11,12].

Previous studies that compared web-based and offline help-seeking among people with suicidal ideation found that people who sought help on the internet reported higher levels of suicidal ideation, indicating that individuals may choose to go on the internet when their suicidality becomes more severe [13,14]. Anonymous digital help can be a low-threshold first step toward professional face-to-face help. In their innovative study, Jaroszewski et al [15] provide evidence that a brief, risk assessment and intervention platform increased crisis service use among those on the internet and in current mental health crisis. Due to their accessible, affordable, and often anonymous nature, digital innovations have the potential to reduce structural barriers to help-seeking. But as Jaroszweski et al [15] state, attitudinal barriers like the preference for informal help remain. It is, therefore, important to develop and evaluate interventions that address those barriers, particularly on digital platforms. However, robust research on reducing barriers to help-seeking in a web-based environment is scarce.

In the Netherlands, the suicide prevention organization “113 Suicide Prevention” provides around-the-clock anonymous support by phone and chat, as well as a web-based self-help course, self-assessment tests, and brief web-based coaching and therapy. Since its opening in 2009, the organization has seen an annual increase in brand awareness and service users, with almost 140,000 chat and phone call conversations and 1.3 million website visits in 2021 [16]. Apart from the homepage, the “test yourself” page is the most visited section of the helpline’s website. Every month, around 4000 people fill in the anonymous self-test for suicidal thoughts. This self-test includes the Suicidal Ideation Attributes Scale (SIDAS) and informs the test-taker of the severity of their suicidal thoughts [17]. Although the vast majority (70%) of people who complete the test score higher than the cutoff point (≥21) for severe suicidal thoughts, only approximately 10% of test-takers go on to navigate to the web page about contacting the helpline. And although due to the anonymity of the helpline’s services, it is not possible to know if people follow up on the advice of contacting the helpline, the difference in demographic distributions between the users of the self-test and the crisis helpline confirms the assumption that a substantial group does not continue using helpline service. While the percentage of men among the self-test users is 40%, it is only around 25% among the users of the helpline [18].

This paper presents the design of a web-based randomized controlled trial (RCT) that aims to reduce barriers to a suicide prevention helpline. The trial is inspired by Jaroszewski et al’s [15] study in which they evaluated a brief, automated barrier reduction intervention (BRI) designed to increase the use of crisis service referrals provided in the mental health app, Koko [19]. Although help-seeking behavior and barriers have been studied in traditional mental health care, guiding reluctant high-risk individuals in web-based environments toward professional help is still relatively uncharted territory. To the best of our knowledge, this study will be the first web-based RCT among people with severe suicidal ideation aimed to reduce the barriers to a helpline. The aim of this study is 2-fold: (1) to measure the effectiveness of a brief barrier reduction intervention (BRI) provided in the self-test motivating people with severe suicidal thoughts to contact the Dutch suicide prevention helpline and (2) to specifically evaluate the effectiveness of the BRI in increasing service use by high-risk groups for suicide such as men and middle-aged people [20].

## Methods

### Study Design

The study is designed as a web-based randomized controlled trial for the anonymous users of a web-based self-test for suicidal thoughts in which individuals with severe suicidal thoughts and no interest in contacting the helpline will be randomly allocated either to a short BRI or receive a general advisory text (care as usual). To minimize the burden on our high-risk and sensitive study population, we aim that it is feasible to complete the intervention within 10 minutes.

### Participants

The participants of the trial will be recruited among the anonymous visitors to the helpline’s website. People who would like to participate will be directed to a web-based information letter and consent form. If they give their consent to the processing of their data for research purposes, the participants will be transferred to the web-based RCT on the survey platform Qualtrics. To assure strict anonymity, no identifying information or IP addresses will be collected.

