### Exclusion Criteria

Participants will be excluded from the study if (1) they are younger than 16 years old, (2) they score below the cutoff point for severe suicidal thoughts (SIDAS score <21), (3) they score above the cutoff point for severe suicidal thoughts (SIDAS score ≥21) and report being likely to contact the suicide prevention helpline. They will be directly transferred to the contact details of the helpline.

People who do not meet the inclusion criteria will be directed to a web page thanking them for their time and encouraging them to contact the helpline if they feel distressed.

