### Sample Size

When assuming probabilities of 0.49 and 0.39 for contacting the helpline for the intervention group and the control group, respectively (based on Jaroszweski et al [15]), a power of .8 and alpha of .05, a sample size calculation for logistical regression analysis (2-tailed) indicates a total sample size of 775 participants [21]. We estimate that about 10% of participants drop out during the intervention; therefore, at least 853 participants have to be included. Furthermore, we estimate that approximately 30% of respondents score below the cutoff point for high risk of suicidal behavior, and based on Jaroszewski et al [15], we expect that 20% of respondents will indicate a high probability of contacting the helpline [15]. We, therefore, estimate that a minimum of 1706 respondents need to be recruited. We will continue to recruit participants until there are enough participants per condition.

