### Procedure

After giving their informed consent and stating that they are 16 years or older, participants will be transferred from the helpline’s website to the Qualtrics platform. Figure 1 displays the study’s flowchart. During the screening phase, respondents start with the self-test. The self-test includes the SIDAS, which consists of 5 items on a 10-point scale measuring the frequency of suicidal thoughts, controllability, closeness to an attempt, distress, and interference with daily activities [17]. The self-test also contains questions regarding gender, age, and if the test-taker is currently in treatment for mental health problems. As mentioned in the exclusion criteria, if respondents score below the cutoff point for severe suicidal thoughts or score above the cutoff point but report that they are likely to contact the helpline, they will be excluded from the RCT.

After inclusion, participants will be randomly assigned to either the intervention or control condition. In both conditions, participants receive a barrier questionnaire to identify the reason why their self-reported likelihood of contacting the helpline in the screening phase was not very likely. After the barrier questionnaire, they receive a general advisory text (control) or an advisory text based on their selected barrier.

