### Statistical Analysis

The analyses will be carried out with an intention-to-treat analysis. Missing values will be imputed using the MICE package in R (v4.2.2; R Core Team 2022) [25]. In order to verify the randomization process and inspect drop-outs, independent *t* tests and chi-square tests will be used to determine whether the control group and the intervention group, as well as the completers and noncompleters, are comparable on baseline factors (ie, gender, age, SIDAS score, and in treatment or not). Chi-square analysis will also be used to test the hypothesis that participants who receive the brief BRI are more motivated to contact the suicide prevention helpline (using the direct link yes/no) than participants in the control condition. To evaluate the effectivity of the BRI in increasing service use by men and middle-aged people, and to examine potential moderators, logistic regression analysis will be used.

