### Ethics Approval

This study protocol is designed in accordance with the relevant guidelines. This research is not subject to the Research Involving Human Subjects Act (Wet medisch-wetenschappelijk onderzoek met mensen) because participants are not subject to procedures and are not required to follow rules of behavior. All participants of the trial will be directed to a web-based information letter and consent form. After giving consent and stating to be 16 years or older, respondents will be transferred to the web-based RCT. No identifying information or IP addresses will be gathered to ensure strict anonymity. This study was reviewed and approved by the Medical Ethics Committee of the Vrije Universiteit Medical Centre (registration number 2021.0443) and is registered at ClinicalTrials.gov (NCT05458830).

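### One person can be randomised more than once, possibly into both arms, and the article describes no way to recognise this; the main risk is dilution of the contrast

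*Protocol article*

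**What the plan says.** All of this is in the protocol article.

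- **Entry.** Under Participants, "The participants of the trial will be recruited among the anonymous visitors" to the helpline's website. The same section adds "To assure strict anonymity, no identifying information or IP addresses will be collected", and Ethics Approval repeats the commitment: "No identifying information or IP addresses will be gathered to ensure strict anonymity".
- **Traffic.** The Introduction describes a standing public test: "Every month, around 4000 people fill in the anonymous self-test for suicidal thoughts".
- **Eligibility.** The list that begins "Participants will be excluded from the study if (1) they are younger than 16 years old" goes on to a SIDAS score below 21, and to a score of 21 or more with stated likelihood of contacting the helpline. It does not mention having taken part before.
- **Allocation.** Under Procedure, "After inclusion, participants will be randomly assigned to either the intervention or control condition". No link to an earlier allocation is described.
- **Recruitment end.** Under Sample Size, "We will continue to recruit participants until there are enough participants per condition".
- **Analysis.** Under Statistical Analysis, "Chi-square analysis will also be used to test the hypothesis that participants who receive the brief BRI are more motivated". The outcome is use of the direct link, yes or no.

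The Limitations section treats anonymity only as an obstacle to follow-up. It does not mention repeat entry.

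**The concern.** Followed as written, a visitor who returns, still scores 21 or more and is still not inclined to call meets every criterion and is randomised again. Under independent 1:1 allocation, about half of such second entries fall in the other arm. Someone who saw the BRI first and the general text second is then counted as a control, although already exposed to the intervention. The reverse order does not contaminate the control arm, but that person is still counted twice.

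At stake are a BRI–control difference pulled towards zero and a count of records that overstates the number of people. This cannot simply be left to a later analysis plan. If nothing is recorded at entry, no analysis can identify the repeats, remove them or test how much they matter.

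**Working it through.** **Inputs from the article.** Rates 0.49 (BRI) and 0.39 (control), two-sided alpha 0.05, power 0.80 and total 775 (Sample Size); 388 per arm (Abstract). **Assumed, not in the article:** the share r of records that are second entries, taken as 2%, 5%, 10% and 20%.

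**1. The plan's own figure.** The pooled two-proportion formula gives 386 per arm, 772 in total. The Wald formula for the log odds ratio gives 776. Both agree with 775. For power at n per arm, with p̄ the mean of the two rates:

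Power = Φ{[(p1 − p0)√n − 1.96√(2p̄(1 − p̄))] / √(p1(1 − p1) + p0(1 − p0))}

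At n = 388 this is Φ{(1.970 − 1.376)/0.698} = Φ(0.850) = 0.802, so there is almost no slack. The increase to 853 is meant for dropout.

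**2. Dilution.** With independent re-randomisation, r/2 of control records come from people who saw the BRI first. If these respond at 0.49 (full carry-over), the control rate becomes 0.39 + (r/2) × 0.10.

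| r | Control rate | Contrast (points) | Power at 388 per arm | Total N for 80% power | Distinct people, 776(1 − r) |
|---|---|---|---|---|---|
| 0 | 0.390 | 10.0 | 0.802 | 772 | 776 |
| 2% | 0.391 | 9.9 | 0.794 | 788 | 760 |
| 5% | 0.3925 | 9.75 | 0.782 | 812 | 737 |
| 10% | 0.395 | 9.5 | 0.760 | 856 | 698 |
| 20% | 0.400 | 9.0 | 0.714 | 956 | 621 |

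**3. Non-independence.** This was simulated with 776 records, 20,000 runs, independent re-randomisation and strong agreement between a person's two responses (parameter 0.8).

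| r | Power | Type I error | Type I error if returners always got the same arm again |
|---|---|---|---|
| 0 | 0.801 | 0.048 | 0.047 |
| 5% | 0.783 | 0.051 | 0.058 |
| 10% | 0.755 | 0.051 | 0.071 |
| 20% | 0.707 | 0.053 | 0.091 |

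A second simulation under independent re-randomisation gave power of 0.787, 0.757 and 0.718 at 5%, 10% and 20%. Power is therefore essentially that of dilution alone. The reason is that same-arm pairs add to the variance of the difference, opposite-arm pairs subtract from it, and with independent allocation the two roughly cancel.

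**4. Dropping repeats without replacing them.** With 388(1 − r) per arm and the undiluted rates 0.49 and 0.39, power is 0.782, 0.760 and 0.710 at 5%, 10% and 20%. Removal restores the contrast but not the power, so first entries must be what counts towards 388.

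**The case against.** **The article is condensed and may omit a safeguard.** This stands in part. The anonymity sentences exclude identifying information and IP addresses. They do not exclude a non-identifying marker or a question about earlier participation. A reader might infer that the trial has nothing to detect repeats; the article supports only that it describes nothing.

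**Repeats may be few.** A repeat must consent twice, again score 21 or more and again report being unlikely to call. The target of 1706 respondents is under half a month of traffic at full uptake (1706/4000 = 0.43). Uptake is not stated, however. Purely as an illustration, 1441 people answered the optional pilot question in 70 days; at that pace 1706 would take 1706/1441 × 70 ≈ 83 days, which leaves time to return. Nothing in the article supports or excludes a 20% share.

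**Full carry-over is generous.** This stands. Every entry is re-screened, and people who now say they are likely to call are excluded before randomisation. Those whom the BRI moved are the most likely to be screened out, so the dilution figures are upper bounds for each r.

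**A reader might infer a false-positive problem or intervals that are too narrow.** The simulation does not support this under independent re-randomisation. Type I error rises only if returners are given the same arm again, which the article does not describe.

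**A reader might also cut n to 388(1 − r) and keep the diluted control rate,** reaching 76%, 72% and 62% power at 5%, 10% and 20%. That counts the loss twice: if the repeats are taken out, their contamination goes with them.

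**Repeats might be thought to be mostly people who did not use the link.** No part of the article shows this, and it is not used here.

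**Conclusion.** The point holds in a limited form. The stated anonymity, the exclusion list and the allocation step together allow one person to be randomised more than once, and no means of detection is described. The consequence is conservative: a contrast pulled towards no effect and fewer distinct people than records, without a material rise in type I error.

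The size depends on a repeat share that the article does not give. At 2% the loss is negligible (power 79%), at 5% it is small (78%), and at 10% and 20% it reaches 76% and 71%. These figures assume independent 1:1 re-randomisation, at most two entries per person, the article's own event rates and full carry-over. The case for acting rests less on any one of these figures than on the fact that the information cannot be recovered once the data are collected.

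**What to change.** 1. Add one anonymous question at consent: *Have you taken part in this study before?*
2. Give those who answer yes the ordinary self-test without re-randomisation.
3. Count only first entries towards the 388 per arm, and restrict the primary analysis to them.
4. Report the number of declared repeats, and name repeat entry among the limitations.

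A non-identifying, session-limited browser marker is optional, and only if it is compatible with the anonymity commitment. Fear of being found out is a barrier reported in the pilot study and listed in the barrier questionnaire, so a lasting marker on a shared device would need care.

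The cost is one question and a sentence in the information letter; no identity or IP address is stored. The downside is that self-report misses some repeats and a few entries are not randomised. If the survey platform already has such a safeguard, one sentence describing it settles the matter.
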